This was deemed necessary because if a patient is completing a set of questions and they need to stop for whatever reason it is helpful for them to be able to recommence from where they left off. For example, an issue may occur with the internet connection or, if the pre-operative data is being collected in a pre-admission clinic setting, a patient may be called away for different appointments mid-way through completing the questions.

If there is an incomplete set of questions recorded, the patient can log back in at any time within a 2-week period to complete the questions. If the questions are not completed within 48 hours of being started the system will send an additional reminder to the patient prompting them to complete the questions. After 2 weeks the session will be locked and the incomplete set of questions will be utilised.

There will be no change to usual medical follow-up (clinic attendance, investigations etc.) except that routine venous imaging is not to be used (currently not recommended and not commonly used).

Aspirin will be administered orally at 100mg (85-150 mg permitted if previously prescribed) daily for 35 (+/-7) days (hips) or 14 (+/-4) days (knees) commencing the day of or day after surgery.

LMWH will be administered as enoxaparin (Clexane) 40mg subcutaneously daily, for 35 days (hips) or 14 days (knees) commencing within 24 hours of surgery. Patients with renal impairment (creatinine clearance of <30ml/min) will be administered enoxaparin (Clexane) in a reduced dosage of 20mg subcutaneously daily and patients undergoing haemodialysis will be treated according to standard local protocol. The reduced dosage of 20 mg will also apply to patients who weigh less than 50 kilograms. Patients who have a contradiction to either study drug will be treated as per local protocols. If this requires the study drug to be withheld the study site will notify the Registry. Patients will be taught to self-administer while in hospital. For those unable to self-administer, the injections will be given by family members, a community nursing service or their local doctor, depending on local arrangements.

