### **3.7. Secondary outcomes**

1. Non-VTE complications (see below)
2. PROMs. Health-related quality of life (EQ5D-5L), Oxford hip and knee scores and patient-rated satisfaction and improvement.
3. Costs. If aspirin is found to be inferior to LMWH, the cost of anticoagulation, cost of hospital stay, need for further health resource utilisation (e.g. nurse or GP visits) and complications will be analysed (see list below)
4. Adherence. Proportion of patients taking the drug continuously (no more than 2 consecutive days missed) for the recommended minimum period.

Non-VTE Complications will be classified into the following groups by the Outcome Verification Committee:

- Readmission related to the original surgery or associated treatment (including bleeding and VTE related) within 90 days
- Reason for readmission (infection, dislocation, stiffness, fracture, wound dehiscence, implant loosening, migration or failure, wound bleeding, other bleeding) within 90 days
- Major bleeding events within 90 days ('major' defined as those resulting in readmission, reoperation or death)
- Reoperation on the same joint within 90 days and 6 months
- Type of reoperation (treatment of infection, reduction of dislocation, manipulation under anaesthesia, fracture treatment, wound repair, implant loosening, migration or failure, non-joint related surgery) within 90 days and 6 months
- Death within 90 days and 6 months

All reports of non-VTE complications will be verified by contact with treating doctors and institutions, except for death, which will be verified through the National Death Index (NDI).

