### 3.8. Participant timeline

| Time Point    | Data Collection Questions and Instruments                                                                                                                                                                                                                                                                                                      |
|---------------|------------------------------------------------------------------------------------------------------------------------------------------------------------------------------------------------------------------------------------------------------------------------------------------------------------------------------------------------|
| Pre-operative | Current anticoagulation use (yes/no and drug)
History of previous VTE
Age
Sex
Joint (hip or knee)
Side
Unilateral vs bilateral
Primary or revision
ASA grade
BMI
Oxford Hip or Knee Score
EQ-5D-5L
EQVAS
Low back pain
Joint pain (numeric rating scale 0-10)
Expectations (pain and improvement) |
| 90 days       | VTE (DVT or PE)
Adherence (did you use pills or injections to prevent a blood clot post-operatively, for how long?)
Current use of anticoagulants (yes/no, which one)
Complications (asked individually, as per complication list)                                                                                                    |
| 6 months      | Complications (asked individually, as per complication list)
Oxford Hip or Knee Score
EQ-5D-5L
Joint pain (scale 0-10)
Satisfaction with outcome of surgery
Patient-rated improvement                                                                                                                                           |

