contraindicated. This will assess the effect of implementing the protocol at a departmental (hospital) level. Other secondary analyses will include an analysis of the subcategories of VTE as the outcome; PE only, all DVT, above knee DVT only and below knee DVT only and non-VTE related complications (death, re-operation, major bleeding and readmission rates). Cluster summary methods will be used for all secondary analyses.

If aspirin is found to be inferior to LMWH, a cost effectiveness analysis of aspirin compared to LMWH will be performed from a health system perspective. Data for resource use associated with treatments and complications will be taken from trial data within the AOANJRR. Survival at one year and quality of life measured using EQ5D at baseline and six months will allow calculation of differences in quality adjusted life years (QALYs) between groups. We will calculate the cost per QALY for each treatment comparison as the difference in mean costs divided by the difference in mean outcomes (quality adjusted survival as QALYs) over the duration of the trial, using regression analysis to adjust for differences at baseline and clustering by site.

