### **Outcome variables**

The primary outcome of the study is symptomatic VTE within 90 days of surgery. Secondary outcomes are:

- Deep vein thrombosis (DVT) only (total, below-knee and above-knee) within 90 days
- Pulmonary embolism (PE) only within 90 days
- Readmission related to the original surgery or associated treatment (including bleeding and VTE-related) within 90 days
- Reoperation on the same joint within 90 days and within 6 months of surgery
- Major bleeding events within 90 days defined as bleeding events resulting in readmission, reoperation or death
- Death within 90 days
- Change in patient-reported pain, function and health status measures as measured by the Oxford Hip Score (OHS), Oxford Knee Score (OKS), EQ-5D score and the EQ-VAS from baseline to 6 months postoperatively

Outcome and demographic data were collected preoperatively (demographics, patient reported pain, function and health status) and at 90 days and 6 months postoperatively. Data for all primary and secondary outcomes are patient-reported (except for death). All patients who responded 'yes' to having experienced a VTE or a secondary operation within 6 months had this result verified by AOANJRR staff through contact with treating doctors and hospitals. A random audit of 200 patients who did not report a VTE event was undertaken to detect the false negative reporting rate. All data collected for registered patients specific to CRISTAL have been outlined in the published protocol [15]. Mortality data were collected through linkage between the AOANJRR and the National Death Index.

In the published protocol [15], mortality was to be measured at 90 days and 6 months. Due to the lack of sensitivity in measuring VTE-related mortality at 6 months, and due to the lag in data availability for mortality, we will only analyse mortality at 90 days [17].

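### The planned QALYs give no weight to clots and bleeds that resolve before the six-month EQ-5D and have no common horizon, so the conditional cost per QALY would be biased and under-specified

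*Supplement*

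**What the plan says.** Final protocol section 3.15 plans a cost-effectiveness analysis from a health system perspective if aspirin is found inferior. Section 2.5 lists it last among the secondary aims.

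- **Utility and survival (3.15).** "Survival at one year and quality of life measured using EQ5D at baseline and six months will allow calculation of differences in quality adjusted life" (QALYs).
- **Ratio (3.15).** Difference in mean costs over difference in mean outcomes, described as "quality adjusted survival as QALYs) over the duration of the trial". The length of that period is not given.
- **Schedule (3.8).** EQ-5D-5L is listed pre-operatively and at 6 months. The 90-day row has VTE, adherence, "Current use of anticoagulants (yes/no, which one) Complications (asked individually, as per complication list"), and no EQ-5D. The description of the instrument says it refers to health on the day of completion.
- **Events (3.6, 3.7).** VTE is assessed at the 90-day follow-up and major bleeding within 90 days. Both are to be verified with treating doctors and institutions.
- **Costs (3.7, 3.3, 3.15).** The cost outcome includes "need for further health resource utilisation (e.g. nurse or GP visits"). For patients unable to self-inject, "the injections will be given by family members, a community nursing service or their local doctor". Resource use is to come from trial data held in the registry.
- **Final SAP.** It has no economic section. On the mortality outcome it says "we will only analyse mortality at 90 days".

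**The concern.** The arms are expected to differ in clots and bleeds during the first 90 days. Take a patient with a clot in week 2 who has recovered by month 6, and another with no clot. They can give the same two EQ-5D scores, so a line drawn between those scores assigns them the same QALYs. The final protocol states no event-specific decrement, no interpolation rule and no decision model that would restore the difference.

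Two further gaps affect the same ratio. One-year survival needs a utility value from month 6 to month 12, and no rule supplies one. Injection support by a community nurse or local doctor falls on one arm only and is a health-system cost, yet no question shown asks who gave the injections or counts visits.

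The analysis is run only if aspirin is inferior. That is when the health lost to extra clots has to be set against any extra cost of LMWH.

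**Working it through.** **No figure to reproduce.** The documents state no QALY, utility or cost-per-QALY value. The design figures used below for scale do reproduce:

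- 2.5% versus 1.5% at two-sided 0.05 and 90% power gives 4,117 per group.
- With ICC 0.01, interperiod correlation 0.008 and 180 per cluster-period, the factor is 1 + 179 × 0.01 − 180 × 0.008 = 1.35.
- 4,117 × 1.35 = 5,558, within 31 × 180 = 5,580 per arm, or 11,160 in all.

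**What two readings can see.** On a straight line from baseline *u0* to six months *u6*, QALYs over half a year are 0.5 × (*u0* + *u6*)/2 = 0.25*u0* + 0.25*u6*. An event that changes neither reading contributes exactly 0.

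**Size of the missed part.** All utility inputs are assumptions. Loss per event = decrement × months/12; loss per patient = that × risk difference.

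| Decrement | Months | Per event | Per patient, 1% difference | Per patient, 2% difference |
|---|---|---|---|---|
| 0.05 | 0.5 | 0.0021 | 0.000021 | 0.000042 |
| 0.10 | 3 | 0.025 | 0.00025 | 0.0005 |
| 0.20 | 3 | 0.050 | 0.0005 | 0.0010 |
| 0.30 | 5 | 0.125 | 0.00125 | 0.0025 |

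**Size of the captured part**, over one year, also on assumed inputs:

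- Deaths: a risk difference of 0.01% to 0.1%, utility 0.8 and 0.9 year lost give 0.0001 × 0.8 × 0.9 = 0.000072 to 0.001 × 0.8 × 0.9 = 0.00072.
- Loss still present at 6 months: a decrement of 0.05 in 10% to 30% of events, 1% difference, six-month value carried to month 12 (weight 0.25 + 0.5 = 0.75). This gives 0.1 × 0.05 × 0.75 × 0.01 = 0.0000375 to 0.3 × 0.05 × 0.75 × 0.01 = 0.0001125.
- Sum: 0.00011 to 0.00083.

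**Effect on the ratio, clots only.** The cost difference cancels, so cost per QALY is inflated by 1 + missed/captured. Take a death difference of 0.05% (0.0005 × 0.8 × 0.9 = 0.00036) and the 3-month rows above:

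- Lower: 1 + 0.00025/(0.00036 + 0.0001125) = 1.5.
- Upper: 1 + 0.0005/(0.00036 + 0.0000375) = 2.3.

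Across the full ranges, the missed share of the total runs from 0.000021/(0.00083 + 0.000021) = 2% to 0.00125/(0.00011 + 0.00125) = 92%.

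**Direction.** Net missed loss against aspirin = (excess VTE risk on aspirin × loss per VTE) − (excess bleeding risk on LMWH × loss per bleed). It is zero when the two products are equal and changes sign beyond that.

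**Horizons side by side.** Survival runs to 12 months and the last utility reading is at 6 (5 to 7) months. The ratio runs over a period with no stated length.

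**Cost source.** The 90-day items in 3.8 and its post-operative question list cover pills or injections, drug, days taken, clots, serious bleeding, further surgery and complications. Injection-days can be derived from these; nurse or doctor visits cannot. Data linkage in 3.17 is planned to test the accuracy of outcome reporting, not to supply costs.

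**The case against.** A reader might infer that the cost-effectiveness aim cannot be answered, or that the ratio is undefined. The documents do not support that. Deaths enter the QALYs, complication resource use is to be costed, and utility loss that persists at 6 months is measured. Recovery from surgery common to both arms largely cancels in the difference. A ratio can be formed; it is biased.

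A reader might also infer that the SAP removes one-year survival. It does not. The SAP sentence limits the clinical mortality outcome, citing poor sensitivity for VTE-related death at 6 months as well as data lag, and the SAP describes no economic analysis. Deaths come from twice-yearly National Death Index linkage and do not depend on patient contact. Lag delays one-year survival but does not make it unobtainable. What stands is the missing utility rule after month 6.

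On costs, the printed questions are not the whole form. Readmission is not among them either, yet it is to be patient-reported. So the supported statement is that no source is listed, not that none exists.

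The magnitude is soft: the assumed range for the missed loss spans about 60-fold (0.00125/0.000021). Sampling error is also large beside it. With an assumed EQ-5D SD of 0.15 to 0.25 and 5,580 per arm, ignoring clustering, the standard error of the six-month component is √(2/5,580) × 0.25 × SD = 0.0007 to 0.0012 QALY. The estimate would be imprecise even without the bias. That limits what the ratio can show, but it does not justify leaving out a loss that could be included.

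Finally, the aim is secondary and conditional, and nothing in the primary or safety conclusions depends on it.

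**Conclusion.** The point holds as a bias and a specification gap in a secondary, conditional analysis. As written, utility lost to VTE or major bleeding that resolves before the six-month EQ-5D is not counted. At the 1% design difference, and on assumed decrements and durations, that is 0.00002 to 0.00125 QALY per patient. It can be as large as the part captured, and on mid-range assumptions with clots alone it would inflate the cost per QALY 1.5- to 2.3-fold. Missed bleeding losses may offset or reverse this, so the net direction is not fixed. The lack of a common horizon and the unlisted source for nurse or GP visits follow from the text and need no assumption. The primary non-inferiority result is unaffected.

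**What to change.** Write a short economic analysis specification before the analysis is run.

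1. **One horizon for survival and utility.** Either keep one-year survival from death-index linkage and state the utility rule for months 6 to 12, or use 6 months for both. Using 6 months credits an early death with less: with 0.9 year lost at one year, only 0.9 − 0.5 = 0.4 year counts, so 0.8 × 0.4 = 0.32 QALY in place of 0.8 × 0.9 = 0.72. Replace the reference to the trial's duration with the chosen period.
2. **Resolved events.** Apply stated utility decrements and durations to verified VTE and major bleeding by event date, with a sensitivity range. End each decrement by the six-month reading so that persisting loss is not counted twice. Adding EQ-5D-5L to the 90-day survey is the alternative for anyone not yet surveyed. Recruitment ceased in December 2020 and the 90-day window closes at 120 days, so by the final SAP of 20 July 2021 that option appears closed.
3. **Injection support.** Cost it over a stated range for the share of LMWH patients needing a nurse or doctor, using the recorded drug and days taken, or name the data source if one exists.

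The cost is reliance on utility values from outside the trial and a little extra analysis. No change to the primary analysis is needed.

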### **3.16. Data monitoring and cleaning**

A separate Data Quality Committee will be established to monitor data management and quality.

A separate safety monitoring committee will not be established and no stopping rules will be used as both interventions are commonly used and recommended treatments. No interim analysis will be performed; this will reduce the chance of early stopping due to spurious findings. Adverse events (separate to complications listed under secondary outcomes) will be monitored by the Trial Management Committee).

### **3.17. Auditing and Data validation**

Positive outcomes (reported VTE) reported by patients will be confirmed by contacting hospitals or treating doctors. These will be adjudicated by the Outcome Verification Committee.

A sample of negative outcomes (patients reporting the absence of VTE) will be verified in a similar manner in a random sample of 200 patients with negative outcomes. Complications will be adjudicated by the Outcome Verification Committee. ANZMUSC will audit the study.

The AOANJRR Data Linkage project will be used to test the accuracy of outcome reporting (readmission, re-operation, drug prescriptions). The AOANJRR also links to the National Death Index (NDI) twice a year (February and September). If a patient, who has participated in the CRISTAL project, is flagged as deceased in the AOANJRR database this can also be transferred to the CRISTAL system and no further contact will be made, reducing distress for families.

## 4. Ethics and dissemination

### 4.1. Ethics approval

The study will be submitted to Sydney Local Health District (RPAH Zone) human research ethics committee for approval. Following approval, the study will be submitted to local ethics committees and Research Governance Offices as required for each site. Refer to the Table 2 for sites.

## 4.2. Amendments

Any modifications to the protocol which may impact on the conduct of the study, potential benefit of the patient or may affect patient safety, including changes of study objectives, study design, patient population, sample sizes, study procedures, or significant administrative aspects will require a formal amendment to the protocol. Such amendments will be agreed upon by the Steering Committee and approved by the Ethics Committee prior to implementation and site notification.

Administrative changes of the protocol are minor corrections and/or clarifications that have no effect on the way the study is to be conducted. These administrative changes will be agreed upon by Trial Management Committee and will be documented in a memorandum. The Ethics Committee/IRB may be notified of administrative changes at the discretion of Trial Management Committee.

## 4.3. Consent to project participation

Individual consent is not being sought for randomisation or use of the study drugs. This is because randomisation is not occurring at the patient level and because both study drugs represent current standard practice. Consent is being sought for the collection and use of patient data, as per standard protocol for the AOANJRR Clinical Trials Platform. The Clinical Trials Platform uses the same consent process (and near identical data collection) as the AOANJRR PROMS Pilot Project which has received ethics approval (Reference: X18-0057 & HREC/18/RPAH/90).

### Consent to AOANJRR Clinical Trials Platform

Consent will be obtained electronically. All data collection for this project is electronic. This provides efficiency and effectiveness (less error) and allows a better way to impart information relevant to the consent process. The participant information and consent form will be displayed on the screen. It contains all elements required for a consent form (see Appendix 1). The information under each statement will be expandable. Patients will be provided the option to 'agree to the statement' or 'learn more'. If the patient agrees they will be navigated to the next statement. If the patient chooses to learn more the additional information will be displayed. Once all statements have been agreed to the patient will be

able to choose whether they give consent or no longer wish to participate in the study. If the patient consents to participate they will be directed to the next page where they can complete the required pre-operative CRISTAL questions relevant to their procedure. If the patient chooses not to consent after the initial registration, then all personal information collected at registration will be deleted from the database. The only data that will be retained is:

- Hospital Name (if available)
- Surgeon Name (if available)
- Date of registration

If the patient elects to withdraw at the time of their post-operative assessment, then no further follow-up will be undertaken.

#### Electronic Consent Process Flowchart

[figure not shown]

#### Consent to share data

After completing the pre- and post-operative CRISTAL questions, patients will be given the option (at each time point) to share their data with their treating surgeon. If the patient consents for their results to be shared the treating surgeon will be able to download patient level data from the CRISTAL system. If patients do not consent to share these data, their information will not be provided to the surgeon.

### Waiver of Consent

We are requesting waiver of consent for two different aspects of this project. Firstly, we require waiver of consent for the 'registration' process which involves getting basic contact information from potential participants so that they can be contacted and formally invited to participate and consent. An identical process of registration has been previously approved for the AOANJRR PROMs pilot. Secondly, we request waiver of consent for randomisation and treatment with the study drugs (the intervention) that make up the CRISTAL project.

Each request for waiver of consent are listed below: firstly, for the 'registration' process (clinical trials platform), and secondly for specific involvement (randomisation and treatment) in the CRISTAL study.

